## Abstract

**Background::**

Rapid globalization and urbanization continue to escalate the burden of non-communicable diseases (NCDs) across the world, disproportionally affecting low- and middle-income countries (LMICs). To date, trials have documented that task-sharing with community health workers (CHWs) can reduce systolic blood pressure (SBP), reduce fasting blood glucose, and achieve smoking cessation. However, most studies have been conducted in rural settings, or focused on managing a single condition, such as hypertension only.

**Methods::**

We propose an open-label, two-armed, community-based cluster randomized controlled trial in Pokhara Metropolitan City of Nepal; the second largest city in Nepal. A total of 30 clusters will be randomized into intervention or control arm in a 1:1 ratio. An individual is eligible if living in Pokhara Metropolitan City and having one or more of the following conditions: hypertension, type 2 diabetes, and tobacco smoking. The participants will be recruited through study team home visits. The intervention group will receive an intervention package “SCALE-NCD” which includes 1) home-based monitoring, referral, and counseling for self-management of hypertension, diabetes and tobacco smoking by Female Community Health Volunteers (FCHVs), and 2) weekly mobile phone messages to promote healthy lifestyle. FCHVs are CHWs in Nepal whose usual tasks are limited to maternal and child health care services. The control group will receive usual care, where there is neither of aforementioned two components. Primary outcomes are change in SBP, change in fasting plasma glucose, and change in smoking cessation, the required sample size for which is 405, 105, and 525 per arm, respectively.

**Discussion::**

This study will inform us of the effectiveness of a FCHV-led, and home-based management of the top three NCD risk factors coupled with weekly mobile phone messages in urban Nepal. Building on the previous studies that measured the efficacy of FCHV-led home-based management of a single NCD risk factor in a small geographical area, this scaled-up study will provide us with the realistic impact that FCHVs may have if they are trained to provide primary care services for management of major NCD risk factors.

**Trial registration::**

ClinicalTrials.gov
NCT06740708. Registered on 2024-12-13

## Administrative information

Note: the numbers in curly brackets in this protocol refer to SPIRIT checklist item numbers. The order of the items has been modified to group similar items (see http://www.equator-network.org/reporting-guidelines/spirit-2013-statement-defining-standard-protocol-items-for-clinical-trials/).

## Introduction

### Background and Rationale {6a}

Non-Communicable Diseases (NCDs) are the leading cause of death and disability across the world. The World Health Organization (WHO) estimates that there are 44 million people die from NCDs each year, accounting for 75% of global deaths.^1^ The number of deaths from NCDs across the globe is projected to increase to 52 million by 2030.^2^ The burden of NCDs is disproportionately occur in low- and middle-income countries (LMICs); 86% of premature deaths from NCDs occur in LMICs, and people in LMICs have 1.5 times higher chance of dying from NCDs than those in high-income countries.^3,4^ As health systems in LMICs are less resourced and not adequately capacitated^5^, a clinically meaningful, cost-effective, and sustainable solution to improve prevention and control of NCDs at population level is much needed.

Nepal is a country with the lowest GDP per capita in South Asia^6^, and the burden of NCDs has rapidly increased over the past two decades as a result of globalization, urbanization, and population aging^7,8^. Global Burden of Disease 2021 reported that tobacco smoking (11.1%), high systolic blood pressure (SBP) (9.1%), and high fasting blood glucose (6.5%) are the top three risk factors contributing to all-cause deaths after air pollution (19.2%) in Nepal.^9^ The WHO Global Report on Hypertension documented that there are 4.8 million hypertensive adults living in Nepal, of which 36.0% were diagnosed, 20.0 % were under treatment with anti-hypertensive medicines, and only 9.0% had achieved the BP control goal of lower than 140/90 mmHg^10^. This is lower than the average for the LMICs (diagnosis 43.1%, pharmacological treatment 32.6%, and control 14.3%)^11^. Similarly, proportions of adults with type 2 diabetes diagnosed by physicians (26.5%), treated with oral hypo-glycaemic medicines (20.7 %), and achieving glycaemic control (6.0%) in Nepal^12^ is lower than the LMICs average.^11^

There are several factors that may contribute to poor control of common NCD risk factors such as hypertension and diabetes in Nepal. Conditions such as hypertension and diabetes do not typically exhibit symptoms in early stages. As a result, patients often seek care only after experiencing severe or fatal cardiovascular events, rather than attending regular check-ups. The other factors include lack of resources and skilled health providers who can screen, diagnose, initiate and titrate medical treatments. Nepal, like many other LMICs faces a severe shortage of physicians, a big proportion of whom migrate overseas for better paid opportunities^13^. Approximately 3 million hypertensive adults in Nepal are unable to receive even three annual physician visits due to the limited number of physicians relative to the growing patient demand.^14^ A wide in-country gap in physician density between urban (i.e. high density) vs rural (low density) areas poses another challenge to meeting the health service demand^15^. Additionally, essential commodities such as functioning diagnostic tools and medicines are not available in every primary healthcare facility, further limiting the ability of trained personnel to provide timely care to control NCDs.

One solution to improve the control of common NCD risk factors at the population-level is task-sharing with trained community health workers (CHWs). Task-sharing is an aspect of contemporary health systems in which some clinical tasks performed by physicians are implemented by trained non-physician health workers, thereby allowing physicians to allocate their time on the advanced tasks that require their specialized skills and knowledge.^16,17^ Task-sharing with trained CHWs has been of particular interest among researchers and policymakers because of their large workforce size^11^, ability to reach community population and identifying those who need medical services through door-to-door home visits, and their historical background in reducing maternal and child mortality through the Integrated Community Case Management (ICCM).^18^ To date, trials have indicated that sharing clinical tasks with trained CHWs can reduce systolic blood pressure^19,20^, fasting blood glucose^21–23^, and tobacco smoking^24,25^. In Nepal, in a cluster randomized control trial, it was demonstrated that sharing screening, referral, and self-management support (i.e. healthy lifestyle counseling) tasks with trained Female Community Health Volunteers (FCHVs); government certified CHWs, reduced mean systolic blood pressure (SBP) by 4.9 mm Hg (95%CI −7.78 to −2.00)^26^ and fasting blood glucose by 27.90 mg/dL (95% CI, −37.62 to −18.18)^27^ at 12-month follow-up. In another cluster randomized controlled trial, a greater smoking cessation rate was achieved among the intervention groups who received FCHVs-led lifestyle counseling to smoking cessation, compared to the control groups receiving usual care at 12 months.^28^

Another potential solution is the adoption of mobile health (mHealth) innovations. mHealth, defined as the use of mobile phones and digital technologies to enhance public health, offers significant opportunities to improve the prevention, diagnosis, and management of NCDs in low-resource settings. By facilitating real-time and remote communication, health education and monitoring, mHealth helps address barriers such as workforce shortages and limited access to healthcare facilities. Previous systematic reviews and meta-analyses have reported favourable outcomes from using text messaging (SMS) interventions for managing hypertension, including promoting lifestyle changes^29^ and improving medication adherence^30^. A cluster randomized controlled trial in Nepal also demonstrated that weekly SMS messages promoting self-management among hypertensive adults attending outpatient units of a tertiary hospital reduced SBP by 6.5 mmHg (95% CI: −12.6 to −0.33) over 12 months.

Despite the mounting evidence, there are still knowledge gaps to be filled. First, most of the existing trials tested the effectiveness of task-sharing with CHWs for the management of a single condition (e.g., hypertension only). As patients are likely to develop multiple NCD risk factors (e.g., hypertension and diabetes) through their life courses, there is a need to assess the effectiveness of task-sharing interventions in which CHWs manage multiple conditions simultaneously. Second, there is a wide implementation gap, i.e. despite promising results from trials, many national CHW programs across the world are yet to have formal roles in NCD management. For example, in Nepal, official roles of FCHVs are still limited to maternal and child health services as per the country’s policy. Therefore, there is a limited understanding of how task-sharing with CHWs can be translated from research to practice, implemented in the real world and sustained over time. Third, there is no study testing the effectiveness of SMS messages for NCDs in community settings in Nepal. Previous studies were done in the outpatient hospital settings only, who may have greater range of comorbidities compared to community population.

### Objectives {7}

The primary objective of this trial is to determine the effectiveness of a packaged intervention containing task-sharing with FCHVs and SMS messaging for management of hypertension, type 2 diabetes, and tobacco smoking on change in systolic blood pressure, fasting blood glucose and smoking cessation, respectively. The secondary objective is to identify demographic and socio-economic factors associated with greater change in systolic blood pressure, fasting blood glucose, and/or smoking cessation.

### Trial design {8}

This is an investigator-initiated, pragmatic, superiority, parallel group (1:1), open-label cluster randomized controlled (c-RCT) trial embedded in a type 2 hybrid effectiveness-implementation research study. While the project contains a qualitative study and an implementation study before and after the trial respectively, this paper describes the protocol of the trial only.

## Methods: Participants, interventions and outcomes

### Study setting {9}

The study will be conducted in Pokhara Metropolitan City, the second most populous city in Nepal after Kathmandu. According to the Census 2021, there are a total of 513,504 residents, of whom 51.8% are female; 19.2% are aged 50 years or older; 88.7% are literate; and 25% of adults work in agriculture.^31^ Pokhara Metropolitan City is divided into 33 administrative units known as “wards” (Figure 1), which will be treated as clusters in this trial. Health services are provided through the following major three systems: the governmental health system, private-owned health system, and NGO or charity-based health services. Within the governmental health system, there are four major tiers: (1) FCHVs provide essential health services through door-to-door home visits. As per the national policy, FCHVs have official roles in maternal and child health services, with no formal responsibilities for NCD management; (2) At health posts (or urban health centres), health assistants or auxiliary health workers can measure BP using digital BP monitors and blood glucose using capillary blood glucose monitors. They can also refill certain oral antihypertensive and hypoglycaemic medicines prescribed by doctors; (3) At least one doctor and a few nurses are available in primary health centres, which usually manage ambulatory cases only. Here, patients can be diagnosed by doctors and initiate or titrate their pharmacological treatments, including getting insulin and other injectable medicines; (4) At the hospitals, doctors with subspecialities are available, where patients can be referred for uncontrolled cases or hospitalized due to severe complications. They can also start pharmacological treatment for smoking cessation. In Pokhara Metropolitan City, there are 656 FCHVs, 26 health posts/urban health centres, two primary health centres, and one district hospital.

### Who will take informed consent? {26a}

Informed consent will be obtained by trained research staff, who are fluent in Nepali (the local language), and have completed an undergraduate program related to health or social sciences. They will participate in a seven-day training programme on ethical practices for human subject research, participant recruitment, screening and consent procedures, and data entry using REDCap. Consent discussions will occur at homes of potential participants, during which trained research staff will present the consent form and obtain signatures if agreed to participate. All participants will receive copies of the signed consent forms. There will be two separate consent procedures in this study. The first is a brief consent for screening, administered to individuals who meet the age criterion of 40–75 years. The second is a full enrollment consent, administered to participants who meet all eligibility criteria, including having at least one of the following conditions: hypertension, diabetes, and/or current tobacco smoking.

### Additional consent provisions for collection and use of participant data and biological specimens {26b}

N/A as there are no ancillary studies planned.

## Interventions

### Explanation for the choice of comparators {6b}

The clusters assigned to the control arm (i.e., comparator) will receive usual care, which reflects standard health services. Under usual care, a participant will not receive home visits by FCHVs to address his or her chronic conditions such as hypertension, diabetes and tobacco smoking. FCHVs may still visit his or her house if there is a periconceptual or pregnant woman, a mother, or a child under five years old in the same household. However, as addressed earlier, their services will be limited to sexual, reproductive, maternal, neonatal, and child health services and will not be extended to chronic conditions such as hypertension, diabetes, and tobacco smoking.

### Intervention description {11a}

Clusters will be randomly assigned to either the intervention arm or the usual care arm for a duration of six months. Participants in the intervention arm will receive a package of intervention named “SCALE-NCD,” which consists of two key components.

The first component is regular FCHV home visits to address hypertension, diabetes, and/or tobacco smoking. Trained FCHVs will visit homes of participants in the intervention arm twice during the trial. Within a month from randomization, participants in the intervention arm will be exposed to the first FCHV visit, during which FCHVs will measure blood pressure, blood glucose, and assess smoking status of participants. FCHVs will also provide motivational-interview-based lifestyle counselling focusing on healthy diet, limiting salt intake, promoting weight loss and physical activities, avoiding harmful alcohol consumption, smoking cessation, and regular blood pressure and/or blood glucose monitoring. The health counselling sessions will not only focus on individual-level risk factors but will also explore structured barriers that may hinder optimal management. For instance, if a participant is unaware of the availability of free antihypertensive medications at primary health centres, FCHVs will provide that information and guide them to access these services. Similarly, if a participant faces challenges in finding a suitable space for physical exercise, FCHVs will offer advice on publicly available recreational centres to support their needs. They will also evaluate medication adherence and refer high-risk individuals to doctors’ office for further assessment. Participants will be exposed to the second FCHV home visit between 4- and 5-months post-randomization, where the contents will be the same as for the first visit.

FCHVs working in intervention clusters will be invited to a 5-day training as these tasks are beyond their routine practices. Trainings will include didactic lectures on risk factors and complications related to hypertension, diabetes, and tobacco smoking, as well as practical sessions focusing on motivational interviews to facilitate behavioural changes (including smoking cessation), blood pressure measurements using digital BP monitors, and blood glucose measurements using glucometers. Only those who successfully pass the final assessment and provided consent will deliver these services in their assigned clusters.

Another component is mobile phone messages. Participants in the intervention arm will receive messages through short message service (SMS) to their mobile phones on a regular basis. The messages will include general health education content, such as advice on maintaining a healthy diet, engaging in physical activity, quitting smoking, and avoiding the harmful use of alcohol, maintaining a healthy weight, and adhering to prescribed treatment. Message contents will be tailored according to each participant’s risk profile. Messages will be sent once a week between 9–10 am, in a 160-character format, based on findings from the qualitative study and co-designing workshop conducted during the first phase of the project and based on our previous pilot study^32^. For participants who are unable to read or do not have a mobile phone, messages will be sent to a participant-nominated family member’s phone. This intervention is designed to maintain healthy behaviours that participants are able to achieve through home counselling by FCHVs. Table 1 below details the components of the intervention.

### Criteria for discontinuing or modifying allocated interventions {11b}

Criteria for modifying allocated interventions will be overseen by a study physician based in Pokhara Metropolitan City, who will be hired specifically for this study. The physician will be accessible 24/7 via a direct phone line throughout the study period to address any concerns that arise from research staff or FCHVs. Additionally, the physician will conduct meetings with FCHVs in the intervention clusters every four months to review any issues identified during home visits. Should the study physician raise any concerns regarding the screening or counselling provided by the FCHVs, the FCHVs will contact the relevant participants to modify their management plan in accordance with the physician’s recommendations.

### Strategies to improve adherence to interventions {11c}

To monitor and improve adherence to the intervention, multiple strategies will be implemented. The importance of fidelity will be explained to FCHVs during the training sessions. FCHVs will carry and fill out a paper-based register documenting each home visit. Field supervisors will review these registers regularly for completeness and provide feedback as needed. The data from the registers will be entered into an electronic database developed in REDCap to enable monitoring. In addition, during the midline and endline evaluation at 3 and 6 months, respectively, participants in the intervention arm will be asked the number of FCHV visits they received. These self-reports will be triangulated with FCHV records to assess fidelity and adherence to scheduled visits. These combined strategies will help ensure that the intervention is delivered as intended and allow timely identification of implementation gaps.

### Relevant concomitant care permitted or prohibited during the trial {11d}

Concomitant care and other interventions will be permitted during the trial. Participants in both the intervention and control arms will be free to seek any care from any health facilities as needed. This approach reflects real-world conditions and supports the external validity of the trial.

### Provisions for post-trial care {30}

To support continuity of care beyond the trial period, the study team will coordinate with Pokhara Metropolitan City to develop a phase-in plan for integrating the SCALE-NCD intervention into the existing health system. All medical devices provided to FCHVs, including digital blood pressure monitors and glucometers, will not be withdrawn at the end of the study. FCHVs will be encouraged to continue providing services for those with hypertension, diabetes, or tobacco smoking after the trial concludes.

### Outcomes {12}

Primary outcomes are mean change SBP (mmHg), fasting plasma glucose (mg/dL), and 30 days tobacco abstinence (yes/no). Secondary outcomes will include change in mean diastolic blood pressure (mmHg), blood pressure control (<140/90 mmHg) (yes/no), HbA1c (%), weight (kg), total cholesterol (mg/dL), high-density lipoprotein (HDL) cholesterol (mg/dL), low-density lipoprotein (LDL) cholesterol (mg/dL), total glycerides (mg/dL), adherence to antihypertensive medicines (yes/no), adherence to hypoglycaemic medicines (yes/no), Fagerstrom Test for Nicotine Dependence (FTND) score, 7-days tobacco abstinence (yes/no), harmful alcohol consumption (yes/no), low salt intake (yes/no), high physical activity (yes/no), high fruits and vegetable intake (yes/no).

### Participant timeline {13}

The intervention will consist of six months of either the SCALE-NCD intervention or usual care. In the intervention arm, participants will receive FCHVs home visits twice, while receiving SMS messages weekly. Study team visits for follow-up data collection will occur at 3 months and 6 months. A schematic diagram is presented in Figure 3.

### Sample size {14}

We calculated the required sample size to achieve 90% power for each of the three hypotheses using PASS 2022 software (v22.0.4), with formulations derived from Campbell and Walters (2014)^33^ and Ahn, Heo, and Zhang (2015)^34^. Sample size was calculated for each outcome using a Bonferroni-adjusted method, and the largest required sample size was selected to ensure adequate power for all outcomes. Given the multiple hypotheses corresponding to three different outcomes, we adjusted for multiple comparisons using a Bonferroni correction and set the significance level at 0.05/3 = 0.017 for each test.

For the fasting blood glucose sample size calculation, we assumed a coefficient of variation (COV) of the cluster size of 0.65, a standard deviation of 45.5^27^ and an intra-class correlation coefficient (ICC) of 0.01.^27^ We determined that sample sizes of 90 in the intervention group and 90 in the control group, obtained by sampling 15 clusters with an average of 6 subjects each, were required to detect a difference between the group means of at least −26 mg/dl. After adjusting for a 15% attrition rate, the participant enrollment from each cluster is 9/0.85 = 7, resulting in a sample size of 105 per arm.

For SBP, we assumed the same COV and ICC as 0.01, with a standard deviation of 15.46.^26^ An average of 23 subjects per cluster per arm would achieve 90% power to detect a difference between the group means of at least −5 mmHg. After adjusting for a 15% attrition rate, the participant enrollment from each cluster is 23/0.85 = 27, resulting in a sample size of 405 per arm.

For smoking cessation, we used the test for two proportions in c-RCTs, with formulations from Donner and Klar (2000). We assumed an ICC of 0.01 and a proportion of smoking quitters in the control group of 0.019.^28^ Sample sizes of 450 per arm, obtained by sampling 15 clusters with 30 subjects each, achieve 80% power to detect a difference between the group proportions of 0.05. After accounting for a 15% dropout rate, we require 35 participants in each group, resulting in a total sample size of 525 per group.

Using Bonferroni-adjustment for each outcome and taking the largest sample size is conservative and may overestimate requirements. Despite the outcomes being correlated, this univariate approach ensures adequate power and simplifies interpretation without assuming a multivariate distribution.

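### The sample size section promises 90% power for each primary hypothesis, but smoking cessation, which sets the trial size, is sized for 80%

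*Protocol article*

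**What the plan says.** All the statements are in the protocol article, Sample size {14}.

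- Opening claim: "We calculated the required sample size to achieve 90% power for each of the three hypotheses". The section says it "set the significance level at 0.05/3 = 0.017 for each test".
- Glucose: "we assumed a coefficient of variation (COV) of the cluster size of 0.65", with an ICC of 0.01, a standard deviation of 45.5, a difference of 26 mg/dL, and 15 clusters per arm averaging 6 subjects. The attrition step reads: "the participant enrollment from each cluster is 9/0.85 = 7, resulting in a sample size of 105 per arm".
- Blood pressure: "For SBP, we assumed the same COV and ICC as 0.01, with a standard deviation of 15.46", a difference of 5 mmHg, an average of 23 subjects per cluster, 90% power.
- Smoking: "We assumed an ICC of 0.01 and a proportion of smoking quitters in the control group of 0.019". No COV is named. The result is given as: "Sample sizes of 450 per arm, obtained by sampling 15 clusters with 30 subjects each, achieve 80% power". The target effect is an absolute gap of 0.05 in quit rates. After 15% dropout this becomes 525 per arm.

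The section takes the largest of the three sample sizes, which is the smoking one (525 against 405 and 105), and describes its approach as conservative. Recruitment {15} samples voters by voting centre, sex and age group. It states no target number of smokers per ward.

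**The concern.** Two statements about the same primary hypothesis disagree: 90% in the opening sentence and 80% in the smoking paragraph. One might be a misprint, so the first question is which figure the 450 per arm supports. The second question is whether the smoking calculation rests on the same footing as the other two, since it alone names no variation in cluster size.

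At stake is the stated type II error for the outcome that fixes enrolment: 20% against the 10% in the opening sentence. Readers and the monitoring board should have one correct figure for each primary outcome.

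**Working it through.** **Inputs** (all from Sample size {14}): control quit proportion 0.019; difference 0.05, so 0.069 under intervention; ICC 0.01; 15 clusters of 30 per arm; alpha 0.05/3. The section does not state sidedness, so a two-sided test is assumed (critical value 2.394).

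**Formulas.** Design effect DE = 1 + [(1 + COV²)m − 1] × ICC, which is 1 + (m − 1) × ICC when COV = 0. Effective n per arm = 15m/DE. SE = √{[p₁(1 − p₁) + p₂(1 − p₂)]/n}. Power = Φ(difference/SE − critical value).

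**1. Reproducing the plan's smoking figure (COV = 0).**
- DE = 1 + 29 × 0.01 = 1.29; effective n = 450/1.29 = 348.8.
- Variance sum = 0.018639 + 0.064239 = 0.082878; SE = √(0.082878/348.8) = 0.01541.
- 0.05/0.01541 = 3.244; power = Φ(3.244 − 2.394) = Φ(0.850) = 80.2%. A pooled-variance version gives 79.7%.

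The printed 80% is therefore the design figure and not a slip for 90%.

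**2. Where 90% would come from.** With the same inputs at an unadjusted two-sided 0.05, power = Φ(3.244 − 1.960) = Φ(1.284) = 90.0%. So 450 per arm supports 90% power or the Bonferroni level, not both.

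**3. The other two outcomes at 0.05/3 with COV 0.65** (SE = SD × √(2/n)).
- Blood pressure, m = 23: DE 1.317, effective n = 345/1.317 = 261.9, SE = 15.46 × √(2/261.9) = 1.351, power = Φ(5/1.351 − 2.394) = 90.4%.
- Glucose, m = 6: DE 1.075, effective n = 90/1.075 = 83.7, SE = 45.5 × √(2/83.7) = 7.03, power = Φ(26/7.03 − 2.394) = 90.4%.

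The opening claim holds for these two, with unequal clusters allowed for.

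**4. Smoking if cluster sizes vary** (m = 30, alpha 0.05/3).

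| COV | DE | Effective n per arm | Power |
|---|---|---|---|
| 0 | 1.290 | 348.8 | 80.2% |
| 0.3 | 1.317 | 341.7 | 79.3% |
| 0.4 | 1.338 | 336.3 | 78.6% |
| 0.65 | 1.417 | 317.6 | 75.9% |

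Other formula variants at COV 0.65 (pooled variance, relative efficiency) give 75.3% to 76.6%.

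**5. What 90% for smoking would take at 0.05/3.** With equal clusters, 43 analysed per cluster (645 per arm). With COV 0.65, 52 to 53 (780 to 795 per arm). If all 525 enrolled per arm were analysed, power would be about 85% (COV 0) or 81% (COV 0.65), still short of 90%.

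**6. The attrition lines.** 9/0.85 = 10.6, not 7. The 6 per cluster stated just before gives 6/0.85 = 7.06, and 7 × 15 = 105, so the 9 is a misprint for 6 and the result stands. For smoking, 30/0.85 = 35.3 is rounded down to 35, which leaves 525 × 0.85 = 446 analysed rather than 450. That costs about 0.3 percentage points of power (80.2% to 79.9%).

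**The case against.** The strongest reply is that the smoking paragraph prints 80% openly, that 450 and 525 per arm agree with it, and that the abstract repeats 525 without claiming any power. On that view nothing is hidden and only one sentence is loose. This stands as far as consequences go: the primary analysis and its type I error are untouched, and a null smoking result would be judged by its confidence interval. It does not rescue the opening sentence, which is wrong for one of the three hypotheses it covers.

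A reader might infer that the true smoking power is 76%, because the wards are the same for all outcomes. The document does not support that as a finding. The glucose and blood pressure paragraphs speak of average cluster sizes, whereas the smoking paragraph fixes 30 in each cluster. The relevant COV concerns analysed smokers per cluster, not ward population, and none is given for smokers. What remains is that Recruitment {15} sets no quota that would produce equal numbers, so the assumption needs a reason.

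A reader might also test these powers against a t distribution on 28 degrees of freedom, which gives lower figures (smoking about 75% with equal clusters). Nothing in the document specifies that reference, and the normal formulas reproduce the stated powers, so no error is shown there. The rounding and the misprint do not change the sample size either.

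**Conclusion.** Wrong as written. The opening claim of 90% power holds for blood pressure and glucose (90.4% each) but not for smoking cessation, where the plan's own inputs give 80.2%. The planned type II error for the outcome that sets the trial size is therefore about 20%, twice what the opening sentence implies. This rests on a two-sided test, an intervention quit proportion of 0.069 and equal clusters.

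The equal-cluster assumption is unexplained rather than shown to be false. If it fails, smoking power falls to about 79% at a COV of 0.3 and about 76% at 0.65.

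It would be going too far to conclude that the trial must be enlarged, or that a null smoking result would be badly misread: 80% is a disclosed design choice. This is a should-fix correction.

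**What to change.** 1. Restate the opening claim as 90% power for blood pressure and glucose and 80% for smoking cessation, each at 0.05/3.
2. Either justify equal cluster sizes for smoking (for example, by stating a per-ward recruitment target for smokers if one exists) or report smoking power under the COV of 0.65, about 76%.
3. Correct 9/0.85 to 6/0.85.

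These are text changes with no added enrolment.

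Optionally, replace single-step Bonferroni by Holm across the three primary tests. Family-wise error stays at 0.05. In simulation with independent tests and both other effects as planned, smoking power rises to about 89% (COV 0) or 86% (COV 0.65). That is close to the best case: about 84% or 80% if one other outcome has no effect, and about 80% or 76%, essentially no gain, if neither does. Holm does not reach 90%, so it does not replace the first correction. Its cost is one sentence and less simple simultaneous confidence intervals. Bonferroni is valid if kept.
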